## Abstract

**Background:**

The aim of the proposed study is to perform a comparative analysis of functional training effects for the paretic upper limb with and without transcranial direct current stimulation over the primary motor cortex in children with spastic hemiparetic cerebral palsy.

**Methods:**

The sample will comprise 34 individuals with spastic hemiparetic cerebral palsy, 6 to 16 years old, classified at level I, II, or III of the Manual Ability Classification System. Participants will be randomly allocated to two groups: (1) functional training of the paretic upper limb combined with anodic transcranial stimulation; (2) functional training of the paretic upper limb combined with sham transcranial stimulation. Evaluation will involve three-dimensional movement analysis and electromyography using the SMART-D 140® system (BTS Engineering) and the FREEEMG® system (BTS Engineering), the Quality of Upper Extremity Skills Test, to assess functional mobility, the Portable Device and Ashworth Scale, to measure movement resistance and spasticity, and the Pediatric Evaluation of Disability Inventory, to evaluate performance. Functional reach training of the paretic upper limb will include a range of manual activities using educational toys associated with an induced constraint of the non-paretic limb during the training. Training will be performed in five weekly 20-minute sessions for two weeks. Transcranial stimulation over the primary motor cortex will be performed during the training sessions at an intensity of 1 mA. Findings will be analyzed statistically considering a 5 % significance level (*P* ≤ 0.05).

**Discussion:**

This paper presents a detailed description of a prospective, randomized, controlled, double-blind, clinical trial designed to demonstrate the effects of combining transcranial direct current stimulation over the primary motor cortex and functional training of the paretic limb in children with cerebral palsy classified at level I, II, or III of the Manual Ability Classification System. The results will be published and evidence found may contribute to the use of transcranial stimulation for this population.

**Trial registration:**

ReBEC RBR-6V4Y3K. Registered on 11 February 2015.

## Background

Cerebral palsy is a term used for motor development disorders stemming from a primary brain lesion that are permanent and mutable, causing secondary musculoskeletal problems and limitations regarding activities of daily living [1]. Motor impairment is the main manifestation of cerebral palsy, leading to abnormal body biomechanics. Children with cerebral palsy may also exhibit intellectual and sensorial impairments, which further restrict functional performance [2, 3].

Depending on the topographic distribution, motor impairment is categorized as tetraplegia when all limbs are affected, which accounts for 9–43 % of cases, diplegia when upper limb involvement is milder than lower limb involvement, which accounts for 10–33 % of cases, and hemiplegia when only one side of the body is affected, which accounts for 25–40 % of cases. The upper limbs are affected in 50–70 % of individuals with cerebral palsy [4, 5], with a highly variable dynamic upper limb movement pattern, depending on the location and extent of the central nervous system lesion. Hemiparesis is a milder form of hemiplegia, characterized by unilateral motor deficiency contralateral to the brain lesion [6, 7]. Together with muscle spasticity, children with hemiparesis exhibit loss of motor neuronal excitation, which is typically associated with poor selective motor control and muscle weakness, resulting in significant functional incapacity [6, 8, 9].

Children with hemiparesis have limitations regarding the use of the affected upper limb and, consequently, two-hand coordination; this exerts a negative impact on activities of daily living and participation at school, in the community, and in family life [10]. Spasticity, muscle weakness, limited supination, and limited reach lead to difficulties with activities involving reaching, grasping, and handling objects. Such problems compromise functional performance, especially among schoolchildren, who are required to demonstrate greater independence in activities related to learning, mobility, and self-care.

Primary upper and lower limb impairment due to spasticity, muscle weakness, and deficient motor control can give rise to secondary musculoskeletal complications, such as contractures and deformities, resulting in restricted movements. Functional limitations can result in motor deficiency, as well as impairments with regard to sensation, perception, cognition, behavior, and communication [4, 11]. According to Darrah et al. [12], functional performance in children with cerebral palsy is determined by a number of factors, such as abnormal muscle tone, the demands of a given task, the severity of the clinical condition, and aspects of the environment. Moreover, motivation, interest, family support, proper adaptations, and opportunities to practice a given task have a positive influence on functional performance in these children. Considering these factors, many therapies are directed toward improving neuromuscular deficiencies with the intention of improving functional performance [4, 13, 14]. Different intensive therapy approaches are currently aimed at improving the performance of the upper limbs. Traditional therapy uses a two-hand training approach; whereas constraint-induced movement therapy has emerged as a promising single-hand training approach [10]. However, a meta-analysis evaluating the efficacy of all non-surgical methods for the upper limb rehabilitation stresses the absence of strong evidence supporting a specific therapy model to improve the functional performance of the affected upper limb in children with hemiparesis secondary to cerebral palsy [15].

### Transcranial direct current stimulation

Transcranial direct current stimulation is a promising non-invasive therapeutic resource for the treatment of children with cerebral palsy in which the motor cortex is stimulated using a low-intensity (1–2 mA), monophasic, direct, electrical current through surface electrodes. The advantages of transcranial direct current stimulation over other transcranial stimulation methods are the longer-lasting modulating effect on cortex function, ease of administration, and lower cost. Moreover, this type of intervention allows better placebo stimulation, thereby conferring greater specificity to scientific findings [16, 17].

The effects of stimulation are achieved by the movement of electrons. The two electrodes are an anode with a positive charge and a cathode with a negative charge. An electrical current flows from the positive to the negative pole and has different effects on biological tissues. Although most of the current is dissipated among the tissues over the cortex during transcranial direct current stimulation, a sufficient amount reaches the cortex structures and modifies the membrane potential of local cells [18, 19].

Transcranial direct current stimulation has short-term effects on cortex excitability when administered for short periods and longer-lasting effects related to plastic mechanisms when administered over a longer period [20]. A number of studies conducted on animal models report the effects of transcranial direct current stimulation on the cerebral cortex, demonstrating that polarized currents administered to the cerebral surface increase spontaneous firing [21] and initiate paroxystic activity [22] when the anodal pole is used, whereas the cathode generally depresses these events. Based on these data, studies involving human beings have evaluated the effects of each pole on cortex excitability through stimulation of the primary motor cortex. Anodal stimulation is reported to increase excitability and cathodal stimulation diminishes excitability [21]. Transcranial direct current stimulation is a neuromodulation technique that has drawn the attention of a large number of researchers in recent years. The findings of clinical studies have demonstrated the potential of this method in the treatment of neurological disorders and the investigation of the modulation of cortex excitability [17].

In the rehabilitation process, the aim of neuromodulation techniques is to increase local synaptic efficacy, thereby altering the maladaptive plasticity pattern that emerges following a cortex lesion. The possibility of combining physical therapy modalities is one of the advantages of transcranial direct current stimulation. Stimulation is a way to modulate cortex activity by opening a path to enhance and prolong functional gains achieved through physical therapy. Stimulation allows a change in a dysfunctional excitability pattern through the activation of specific neural networks so that physical therapy can mold a functional cortex activity pattern [17]. Studies involving the use of transcranial direct current stimulation over the primary motor cortex in stroke victims have demonstrated improvements in upper limb function (active wrist and finger movements), movement velocity, active ankle movements, and overall motor function. However, only a very small number of studies have analyzed the effects of transcranial stimulation in children with cerebral palsy. The literature reports the use of transcranial magnetic stimulation as a way to analyze evoked potentials [23, 24] and as a resource to reduce spasticity in children with cerebral palsy [25, 26].

Analyzing the effects of transcranial magnetic stimulation, a recent study [27] reports significant changes in motor cortex maps in children with hemiparesis or diparesis stemming from cerebral palsy, such as lateral movements of the affected upper limb and motor representation of the affected lower limb, demonstrating reorganization following lesions in one or both hemispheres of the brain. Another recent study [28] employed transcranial direct current stimulation combined with treadmill training in a child with cerebral palsy and found beneficial effects with regard to the acquisition of motor skills. Another study [29], involving children with congenital hemiparesis, concluded that transcranial direct current stimulation appears to be safe, feasible, and well tolerated in most children with hemiparesis, but the authors of that study suggest further investigations of serial sessions of transcranial direct current stimulation in conjunction with rehabilitation for a synergistic approach to improving hand function.

## Methods/design

### Primary objective

The primary objective of the proposed study is to analyze manual ability before and after functional training of the paretic upper limb with anodic and sham transcranial direct current stimulation over the primary motor cortex (ipsilesional hemisphere) in children with spastic, hemiparetic cerebral palsy, classified at levels I, II, or III of the Manual Ability Classification System [30].

### Hypothesis 1

Functional reach training of the paretic upper limb with anodic transcranial direct current stimulation over the primary motor cortex will achieve greater effects in comparison to functional reach training with sham transcranial direct current stimulation in children with spastic, hemiparetic cerebral palsy classified at level I, II, or III of the Manual Ability Classification System [30].

### Study design

A prospective, paired, randomized, controlled, double-blind clinical trial is proposed (Fig. 1). The protocol for this study is registered with the Brazilian Registry of Clinical Trials (ReBEC) RBR-6V4Y3K.

**Fig. 1 Fig1:**
[figure not shown]
Flowchart of the study following Consolidated Standards of Reporting Trials (CONSORT) guidelines. tDCS, transcranial direct current stimulation

### Recruitment and sample selection

Individuals with hemiparetic cerebral palsy will be recruited from the physical therapy clinics of the Nove de Julho University, São Paulo, Brazil, and will be selected based on the following eligibility criteria.

### Inclusion criteria

Diagnosis of spastic, hemiparetic cerebral palsyFunctional classification at level I, II, or III of the Manual Ability Classification System [30]Aged 6 to 16 yearsAdequate understanding and cooperation during the proposed activitiesStatement of informed consent signed by a legal guardian

### Exclusion criteria

Having undergone surgical procedures or neurolytic block in the 12 months prior to the onset of the training sessionsOrthopedic deformity with indication for surgeryEpilepsyMetal implant in the skull or use of hearing aids

### Sample size

The sample size was calculated using the STATA 11 program, using a study conducted by Choudhary et al. [31] as the basis. Scores on the Quality of Upper Extremity Skills Test (QUEST) were used for the calculation. Based on the mean and standard deviation values of the experimental group prior to intervention (mean: 76.4; standard deviation: 9.2) and after the intervention (mean: 87.2; standard deviation: 9.4), a bidirectional alpha of 0.05 and 80 % test power, a minimum of 13 children were deemed necessary for each group. The sample will be increased by 20 % to compensate for possible dropouts, leading to 17 children in each group (overall sample: 34 participants).

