### Randomization

Children who meet the eligibility criteria will be randomly allocated to one of the two study groups using block randomization.

### Group 1

This group will receive the intervention, that is, functional reach training of the paretic upper limb with range manual activities combined with active transcranial direct current stimulation over the primary motor cortex of the ipsilesional hemisphere.

### Group 2

This will be the ‘control’ group and will receive functional reach training of the paretic upper limb with range manual activities combined with sham transcranial direct current stimulation over the primary motor cortex of the ipsilesional hemisphere.

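### The 80% power rests on one arm's before-to-after QUEST change, so it is unsupported for the active-versus-sham comparison

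*Protocol article*

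**What the plan says.** The Sample size section takes its inputs from one arm of one cited study: "mean and standard deviation values of the experimental group prior to intervention (mean: 76.4; standard deviation: 9.2) and after the intervention". The later score is given as 87.2, with an SD of 9.4. With "a bidirectional alpha of 0.05 and 80 % test power", the section concludes that "a minimum of 13 children were deemed necessary for each group". It then adds: "The sample will be increased by 20 % to compensate for possible dropouts, leading to 17 children in each group". It gives no control-arm value, no difference between arms and no pre-post correlation.

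The trial's question is a comparison between arms. Hypothesis 1 is that training with active stimulation "will achieve greater effects in comparison to functional reach training with sham transcranial direct current stimulation". Under Randomization, the control group "will receive functional reach training of the paretic upper limb with range manual activities combined with sham transcranial direct current stimulation". The training protocol, including constraint of the non-paretic limb, makes no exception for the sham arm. The Statistical analysis section compares active with sham by ANCOVA adjusted for baseline, under intention to treat, with last observation carried forward for missing follow-up values.

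**The concern.** A before-to-after change in one arm contains everything that moves the score: training, practice, time and whatever else that arm received. The trial aims to isolate what stimulation adds to training that both arms share. These are different quantities, and the document offers nothing that turns the first into the second.

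At stake is how the result is read. A non-significant difference, read beside a claim of 80% power, invites the conclusion that stimulation adds nothing. That inference is sound only if the power refers to a between-arm difference that someone has justified.

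**Working it through.** **Inputs from the Sample size section.** Means 76.4 and 87.2; SDs 9.2 and 9.4; two-sided alpha 0.05; power 80%; 13 per group, raised to 17.

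**Reproducing the stated figure**

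- Difference: 87.2 − 76.4 = 10.8.
- Pooled SD: √[(9.2² + 9.4²)/2] = 9.30.
- Two independent groups, normal formula: n = (1.960 + 0.842)² × (9.2² + 9.4²)/10.8² = 11.6, rounded up to 12.
- Two-sample t test: n = 12.68, rounded up to 13. Power is 77.6% at 12 per group and 81.1% at 13.
- Dropout: 13/(1 − 0.20) = 16.25, rounded up to 17, as stated.

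The two-sample t calculation, with the two time points as separate groups, returns the stated 13. A paired t test with SD of change √(9.2² + 9.4² − 2ρ × 9.2 × 9.4) needs 8, 6 or 5 children at assumed correlations ρ of 0.5, 0.7 or 0.8. It returns 13 only at a correlation near 0.1. Even then it would size a before-after test in one group, not active versus sham.

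**Power for the trial's own comparison**

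The document gives neither the between-arm difference D nor the correlation ρ, so both are assumptions here. For illustration, D is 8.1 or 5.4, that is, three quarters or half of 10.8. The residual SD under ANCOVA is 9.30 × √(1 − ρ²), which is 8.05, 6.64 and 5.58 for ρ = 0.5, 0.7 and 0.8. Power comes from the noncentral t distribution with noncentrality D/[SD × √(2/n)].

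Example: D = 5.4, ρ = 0.7, n = 13. The standard error is 6.64 × √(2/13) = 2.60, the noncentrality is 5.4/2.60 = 2.07, and power is 51%.

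| D | n per arm | unadjusted | ρ = 0.5 | ρ = 0.7 | ρ = 0.8 |
|---|---|---|---|---|---|
| 8.1 | 13 | 57% | 69% | 84% | 94% |
| 8.1 | 17 | 69% | 81% | 93% | 98% |
| 5.4 | 13 | 30% | 37% | 51% | 66% |
| 5.4 | 17 | 38% | 47% | 63% | 78% |

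Entries can move by about one percentage point with rounding or with SD 9.4 in place of 9.3.

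**Between-arm difference detectable with 80% power (QUEST points)**

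| n per arm | unadjusted | ρ = 0.5 | ρ = 0.7 | ρ = 0.8 |
|---|---|---|---|---|
| 13 | 10.7 | 9.2 | 7.6 | 6.4 |
| 17 | 9.2 | 8.0 | 6.6 | 5.5 |

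**The case against.** The strongest reply is that the planned analysis is not an unadjusted t test. Baseline adjustment recovers power, and intention to treat with values carried forward means that up to 17 per arm would be analysed. This largely stands. At 8.1 points, five of the six ANCOVA cells reach 80%. A reader might infer that power falls far below 80% as soon as the sham arm improves; the document does not support that. What remains is that at 5.4 points all six cells stay below 80%, and that the sample-size section claims no gain from adjustment. Carried-forward values may also dilute the effect, so 17 per arm is not automatically the right basis.

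A reader might also infer that the plan assumes no improvement at all under sham. That follows only if the active arm gains exactly 10.8 points. A 10.8-point difference could also arise if active gains more and sham gains something. The section does not say what the cited study's experimental intervention was, so what its 10.8 points represent cannot be judged here.

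Finally, the document does not state which formula was used, and the study design is described as paired. The independent-groups route is by far the more plausible, because it reproduces 13 directly, but it is an inference. The point does not depend on it: neither route uses an active-versus-sham difference.

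**Conclusion.** The power statement is wrong as written. The arithmetic and the dropout step are sound, but the effect entered is a within-arm change, and no between-arm difference is justified anywhere in the document. The 80% is therefore unsupported for active versus sham.

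It is not shown that power is below 80%. Across the assumed differences of 5.4 and 8.1 points and correlations of 0.5 to 0.8, ANCOVA power runs from 37% to 94% with 13 per arm and from 47% to 98% with 17. These ranges rest on an SD of 9.3 taken from the cited study and on differences and correlations that the document does not give.

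**What to change.** Keep N = 34 and reword the sample-size section:

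- Withdraw the statement that 13 per group gives 80% power for this comparison.
- State that 10.8 points is a within-arm change, not a difference between arms.
- Report what the design can detect. Suggested text: *With 13 children per arm, 80% power corresponds to a between-arm QUEST difference at post-treatment of 10.7 points unadjusted, or 9.2, 7.6 or 6.4 points under ANCOVA with pre-post correlations of 0.5, 0.7 or 0.8. With 17 per arm the values are 9.2 points unadjusted, or 8.0, 6.6 or 5.5 points. The SD of 9.3 comes from the reference study; the correlations are assumptions.*
- State that a non-significant result will be interpreted through the confidence interval for the between-arm difference, set against these values.

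The cost is a less favourable power statement. No extra patients are needed, and neither the analysis nor the conduct of the trial changes.

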### Randomization

Children who meet the eligibility criteria will be randomly allocated to one of the two study groups using block randomization.

### Group 1

This group will receive the intervention, that is, functional reach training of the paretic upper limb with range manual activities combined with active transcranial direct current stimulation over the primary motor cortex of the ipsilesional hemisphere.

### Group 2

This will be the ‘control’ group and will receive functional reach training of the paretic upper limb with range manual activities combined with sham transcranial direct current stimulation over the primary motor cortex of the ipsilesional hemisphere.

### Allocation concealment

The children will be randomly allocated to the two groups. To minimize the risk of an imbalance in the size of the groups, a randomization list will be generated using five blocks of six participants, with three participants in each block randomly allocated to each group, and one block of four participants, with two participants in each block randomly allocated to each group. The allocation sequence will be stipulated in sequentially numbered, sealed, opaque envelopes. Following the baseline evaluation, each participant will be allocated to one of the groups by opening an envelope. This process will be performed by a member of the research team who is not involved in the recruitment process or other aspects of the study.

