### Intervention

#### Transcranial direct current stimulation

Transcranial direct current stimulation will be administered using a DC-STIMULATOR (NeuroConn, Germany) with two sponge (non-metallic) electrodes measuring 25 × 25 cm^2^ moistened in saline solution. The participants will be randomly allocated to active or sham transcranial direct current stimulation over the primary motor cortex following the procedures described by Fregni et al. [17]. The anodal electrode will be positioned over C3/C4 (international 10-20 system of electrode placement), corresponding to the primary motor cortex. The cathode will be positioned in the supraorbital region contralateral to the anode. The anode will be positioned over the primary motor cortex of the contralateral hemisphere to motor impairment. A current of 1 mA [43] will be administered for 20 min in each session. The device has a knob that allows the operator to control the intensity. Stimulation will be gradually increased to 1 mA in the first 10 s and will be gradually diminished in the last 10 s of the session. For sham stimulation, the electrodes will be placed in the same positions and the stimulator will be switched on for 30 s to give the participants the initial sensation, but no stimulation will be administered during the rest of the session. This is a valid control procedure in studies involving transcranial direct current stimulation.

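### The fixed, disclosed block structure would let about 5 to 9 of the 34 allocations be deduced with certainty if staff who deliver the stimulation have any part in enrolment

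*Protocol article*

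**What the plan says.** All references are to the protocol article.

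- **List.** Under Allocation concealment, "a randomization list will be generated using five blocks of six participants, with three participants in each block randomly allocated to each group". A single smaller block, of four children split two and two, completes the list. No random variation of block size is described, and the place of the block of four in the list is not given.
- **Concealment.** In the same section, "The allocation sequence will be stipulated in sequentially numbered, sealed, opaque envelopes". On timing: "Following the baseline evaluation, each participant will be allocated to one of the groups by opening an envelope". The task falls to "a member of the research team who is not involved in the recruitment process or other aspects of the study".
- **Setting.** Under Recruitment and sample selection, children "will be recruited from the physical therapy clinics of the Nove de Julho University". No stratification is stated, so one list serves the whole trial. Trial status says that recruitment was open when the article was submitted.
- **Delivery.** Under Transcranial direct current stimulation, "The device has a knob that allows the operator to control the intensity". For sham, the stimulator is on for 30 s and then gives no current for the rest of the session.
- **Blinding.** The trial is called double-blind. The only staff named as blinded are the evaluating physiotherapists and raters.

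**The concern.** Envelopes conceal the next allocation only while it cannot be worked out from earlier ones. With blocks of known size, each balanced between the arms, the rest of a block is settled once one arm has used up its places. Someone who has seen the earlier allocations then knows the next arm before the envelope is opened.

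The person at the stimulator is the likely holder of that knowledge. The described sham requires someone to stop the current after 30 s, and the article mentions no coded or automated delivery. The separation under Allocation concealment covers only the person who opens the envelopes.

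There is also room to act on such knowledge. One inclusion criterion, adequate understanding and cooperation, is a matter of judgement, and the order in which children reach baseline can be influenced. If enrolment were steered in this way, the arms could differ in traits such as cooperation. The planned analysis of covariance adjusts for baseline values of the outcomes and would not fully correct for an unmeasured trait.

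**Working it through.** **Inputs.** Five blocks of six (3:3) and one block of four (2:2), from Allocation concealment; 34 children, 17 per group, from Sample size.

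**The plan's own figure.** 5 × 6 + 4 = 34 children and 5 × 3 + 2 = 17 per group. The list fits the stated sample size exactly.

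**Certain allocations in a block of six.** There are 20 equally likely orders of a 3:3 block. An allocation is certain when it and all later ones in the block belong to the same arm.
- 6th place: always, probability 1.
- 5th place: the last two are alike, 8/20 = 0.4.
- 4th place: the last three are alike, 2/20 = 0.1.
- Mean: 1 + 0.4 + 0.1 = 1.5.

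**Certain allocations in a block of four.** There are 6 orders.
- 4th place: probability 1.
- 3rd place: 2/6 = 0.33.
- Mean: 1.33.

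**Whole list, block order and all past allocations known.** 5 × 1.5 + 1.33 = 8.83 of 34, or 26%. The minimum is 6 (one per block) and the maximum is 5 × 3 + 2 = 17.

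**Best guess.** Always naming the arm with more places left gives, for a block of 2m, an expected m + 2^(2m−1)/C(2m, m) − 1/2 correct.
- m = 3: 3 + 32/20 − 0.5 = 4.1.
- m = 2: 2 + 8/6 − 0.5 = 2.83.
- Total: 5 × 4.1 + 2.83 = 23.3 of 34, or 69%, against 17 (50%) by chance.

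**Position of the block of four unknown.** A 2:2 split after four children may be a finished block of four or an unfinished block of six, so fewer allocations are certain. In 20,000 simulated lists, with the block of four equally likely in each of the six positions and a guesser who updates by Bayes' rule, 5.3 of 34 (16%) were certain. The best-guess rate was still 68.6%.

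**Randomly varied block sizes.** Each set was simulated with 4,000 lists of 34, sizes equally likely. The guesser knew the set of sizes and all past allocations, but not the sizes drawn.

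| Block sizes | Certain, of 34 | Best-guess rate |
|---|---|---|
| Stated list, order known | 8.8 (26%) | 69% |
| Stated list, position of the four unknown | 5.3 (16%) | 69% |
| 4, 6 | 1.9 (6%) | 69% |
| 2, 4, 6 | 1.3 (4%) | 70% |
| 4, 6, 8 | 0.8 (2%) | 68% |

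Varied sizes remove most of the certainty but hardly change the success of guessing. For someone who does not know past allocations, no allocation is predictable under any of these schemes.

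**The case against.** The strongest reply is that the route to bias needs a link that the article does not supply: someone who knows past allocations must screen, judge eligibility or schedule, or must inform someone who does. Who does these tasks is detail that a full protocol may settle, and silence in an article is not evidence of a fault. The stated safeguards are also good ones. The envelopes are opaque, sealed and numbered, the opener has no other role, and allocation follows baseline, which normally protects against selective entry. All of this stands, so the point is conditional. It does not remove the point, because the fixed block structure is stated, and envelopes do not block deduction from past allocations.

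Four stronger readings are tempting and are not supported:
- A reader might infer that the operator is known to be aware of every past allocation. The text gives only the manual control and the 30 s sham. That makes blindness hard to maintain, but it is an inference.
- A reader might take the block of four as the last, which would make 26% the figure. Its position is not stated, hence the range from 16%.
- A reader might picture a single clinic. The text names clinics, in the plural, of one university.
- A reader might conclude that the block sizes became public during recruitment. Trial status dates open recruitment only to submission.

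The calculated shares are also upper limits. They assume that every earlier allocation is known before the next child is screened, and overlapping enrolment would lower them.

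**Conclusion.** The concern holds in a limited, conditional form. The article fixes and discloses the block structure of one list of 34, and separates only the envelope opener from recruitment. If staff who deliver stimulation know past allocations and take part in or inform screening or scheduling, on average about 5 of 34 allocations (16%, position of the block of four unknown) to 9 of 34 (26%, block order known) could be deduced with certainty despite the sealed envelopes. Most allocations would stay uncertain.

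This rests on three assumptions: that delivery staff are in practice unblinded, that they have some influence on enrolment, and that they know all earlier allocations and the block sizes. The documents state none of these three about the staff. Nothing shows that any allocation has been predicted or any enrolment steered, and no effect on the trial's outcomes can be estimated. The 69% best-guess rate is not a measure of what varied blocks would cure, since it stays at about 68% to 70% with them. This is a cheap improvement of minor priority, not a flaw that undermines the trial.

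**What to change.** 1. For children not yet allocated, have the list holder generate the remaining sequence with randomly varying block sizes, for example 2, 4 and 6, not disclosed to the clinical team or in public text until recruitment closes. Over a full list of 34 this would bring certain allocations down to about 1.3 (4%). The actual gain depends on how many children remain, which the article does not say.
2. Add one sentence under Allocation concealment: staff who deliver stimulation take no part in screening, eligibility decisions or scheduling, and do not pass on allocations to those who do. This matters more than the first step, because it also deals with informed guessing, which varied sizes leave almost unchanged.

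The cost is a new list and envelopes for the remaining children and one sentence of text. With blocks of up to six, the arms could differ by up to three children if recruitment stops within a block.
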